### Withdrawal of study participants

Study participants can leave the study for the following reasons:On the own request of the patientOn the direction of the investigator, if a further participation at the trial may be disadvantageous for patient’s healthIf exclusion criteria become knownPregnancyNon-compliance

The investigator can decide to withdraw a participant from the study for the above mentioned reasons. This will be documented in the case report form (CRF) and the physician is required to notify the Coordinating Investigator. In all cases, the reason for withdrawal must be recorded in the CRF and in the patient’s medical record. All patients who discontinue because of adverse events or clinical laboratory abnormalities should be followed up until they recover or stabilize, and the subsequent outcome should be recorded.

### Replacement of study participants

Patients who underwent randomization and were withdrawn will not be replaced.

### Stopping rules for the whole trial

New risks for subjects become known.Medical or ethical reasons affecting the continued performance of the trial.

### Endpoints

#### Primary endpoint

Primary endpoint is the increase of the IPSS by at least 5 points observed 12 months after surgery compared to the preoperative IPSS per patient. In case of postoperative urologic treatment for newly developed urinary dysfunction, primary endpoint is the increase of the IPSS by at least 5 points observed before urologic treatment compared to the preoperative IPSS. The primary endpoint is based on previous findings [16]. In a group of 61 patients undergoing mesorectal excision for rectal cancer we observed long-term urinary deterioration in 13 patients determined by the IPSS. The median difference in the IPSS was 6 points (range: 1-25 points, interquartile range: 4-8 points). Answers to additional questions on the Qol ranged from 0 (delighted) to 6 (terrible). We found that an increase of the IPSS by at least 5 points leads to a clear decrease in patients’ quality of life due to urinary symptoms (median difference in the Qol score was 3 points (interquartile range: 2-4 points)).

#### Secondary endpoints

Secondary endpoint is the reduction of FSFI/IIEF by at least 8/15 points 12 months after surgery compared to the preoperative FSFI/IIEF per patient. The secondary endpoint is analyzed separately for men and women. No confirmatory analyses are planned for this endpoint. Another secondary endpoint is the change of the WVS observed 12 months after surgery compared to the preoperative score per patient. For assessment of safety, especially oncologic safety adverse events, the rates of pCRM-positive specimen (distance of tumor from circumferential resection margin ≤ 1 mm) and the quality of TME will be documented. The quality of the mesorectum is scored using the M.E.R.C.U.R.Y. grading (Grade I: complete; Grade II: nearly complete; Grade III: incomplete) [17].

### Randomization and blinding

All patients who meet the inclusion criteria will be randomized. Randomization ratio is 1:1 to TME with pIONM or TME without pIONM (Fig. 1). Randomization is stratified according to neoadjuvant therapy and gender using blocks of variable length. Central randomization via FAX is conducted in this study.

**Fig. 1 Fig1:**
[figure not shown]
Summary of study interventions/flow diagram. † In patients who did not undergo stoma closure, study visits are planed 6 and 12 months after TME. Assessment of IIEF/FSFI and WVS will not be carried out. NT: Neoadjuvant therapy, TME: Total Mesorectal Excision, SC: Stoma closure, IPSS: International Prostate Symptom Score, Qol: Quality of life due to urinary symptoms, IIEF: International Index of Erectile Function, FSFI: Female Sexual Function Index, WVS: Wexner-Vaizey Score, pIONM: pelvic intraoperative neuromonitoring

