## Methods/design

### Objectives

The primary objective of this trial is to assess urinary functional outcome in rectal cancer patients undergoing TME with pIONM, when compared to TME without pIONM, in a 12 months follow-up period per patient. The secondary objectives are to assess sexual and anorectal functional outcome in rectal cancer patients undergoing TME with pIONM, when compared to TME without pIONM, in a 12 months follow-up period per patient and to assess the safety, especially oncologic safety and quality of TME.

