### Prescreening / Screening and follow up

In patients undergoing neoadjuvant therapy a prescreening is scheduled 21 to 1 day before therapy begins. The preoperative screening (baseline) is scheduled 14 to 1 day before TME. Study visits and follow up are summarized in Fig. 2.

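### IIEF and FSFI are skipped in patients without stoma closure, so the descriptive sexual-function comparison rests on a subset defined after randomisation

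*Protocol article*

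**What the plan says.** The rule stands in the footnote to Fig. 1 of the protocol article. It first sets the schedule, "In patients who did not undergo stoma closure, study visits are planed 6 and 12 months after TME", and then limits its content: "Assessment of IIEF/FSFI and WVS will not be carried out". IPSS and the urinary quality-of-life item are not among the omitted instruments.

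The other sections do not mention this limit:

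- Objectives: the aim is "to assess sexual and anorectal functional outcome in rectal cancer patients undergoing TME with pIONM, when compared to TME without pIONM".
- Endpoints, on sexual function: "Secondary endpoint is the reduction of FSFI/IIEF by at least 8/15 points 12 months after surgery". Change is measured per patient from that patient's own score before the operation. The same section says that no confirmatory analysis is planned for it and that men and women are analysed separately.
- Statistical analysis: the proportions reaching the 15-point (IIEF) and 8-point (FSFI) thresholds at 12 months are to be shown by arm. The ITT population is defined by availability of IPSS before and after surgery. Last observation carried forward is specified for IPSS.

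On timing, Randomization and blinding states "Randomization ratio is 1:1 to TME with pIONM or TME without pIONM", and Prescreening / Screening and follow up states "The preoperative screening (baseline) is scheduled 14 to 1 day before TME".

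**The concern.** WVS measures anal continence, so leaving it out while a stoma is in place is understandable. Outcome measures describes FSFI and IIEF as questionnaires on sexual function that patients complete themselves, and gives no reason why an open stoma would prevent their use. The footnote nevertheless treats all three instruments alike.

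Two things are at stake. First, the trial gives up sexual-function outcomes in patients who attend at the endpoint time and whose baseline should exist, since the exclusion criteria bar patients with missing preoperative urogenital data. Second, stoma closure comes after TME and hence after allocation. Restricting the comparison to patients with closure conditions on a post-randomisation event, and the endpoint and analysis sections do not tell the reader so.

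**Working it through.** The article states no figure for this point, so there is none to reproduce. The check compares the sections and then sizes the loss under stated assumptions.

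**1. Who has what at 12 months**

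| Item | Stoma closed | Stoma not closed | Source |
|---|---|---|---|
| 12-month visit | yes | yes | Abstract; Fig. 1 footnote |
| IPSS | yes | not listed as omitted | Fig. 1 footnote |
| IIEF/FSFI | yes | no | Fig. 1 footnote |
| In scope of the sexual-function objective | yes | yes | Objectives |
| Can be in the ITT population | yes | yes, through IPSS | Statistical analysis |

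A patient without closure can thus be in the ITT population, be within the stated objective, attend at 12 months, and still have no sexual-function outcome. No other section reverses the footnote.

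**2. Number of patients lost**

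Inputs: 188 patients allocated, 164 needed for the primary analysis, 12% overall dropout (all from Sample size calculation). The non-closure rate f is assumed, because the article gives none. Formula: lost = N × f.

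- f = 10%: 188 × 0.10 = 18.8, about 19 (of 164: 16)
- f = 20%: 188 × 0.20 = 37.6, about 38 (of 164: 33)
- f = 30%: 188 × 0.30 = 56.4, about 56 (of 164: 49)

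For scale, the planned dropout is 188 × 0.12 = 22.6, about 23 patients. That allowance was made for the primary endpoint; the descriptive endpoint has no power target to miss.

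**3. Precision**

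If the loss is spread evenly, confidence intervals widen by a factor 1/√(1 − f): 1/√0.9 = 1.05, 1/√0.8 = 1.12, 1/√0.7 = 1.20. This applies within each sex-specific analysis, which is already smaller than the whole trial.

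**4. When bias arises**

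Illustration with every rate assumed. pIONM has no effect on sexual function. The endpoint risk is 40% in patients who would have closure under either arm and 70% in all others. Non-closure is q_c in one arm and q_t ≤ q_c in the other, and everyone who closes in the first arm would also close in the second. The observed risk is 0.40 in the arm with fewer closures. In the arm with more closures it is

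[(1 − q_c) × 0.40 + (q_c − q_t) × 0.70] / (1 − q_t).

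- 20% vs 20%: 0.320/0.80 = 0.400, difference 0
- 20% vs 15%: (0.320 + 0.035)/0.85 = 0.418, difference +1.8 percentage points
- 20% vs 10%: (0.320 + 0.070)/0.90 = 0.433, difference +3.3 points
- 30% vs 20%: (0.280 + 0.070)/0.80 = 0.4375, difference +3.75 points

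The spurious difference counts against the arm with more closures. It vanishes when the same kind of patient closes at the same rate in both arms.

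**The case against.** The strongest reply is that little depends on this. The endpoint is secondary and descriptive, and the confirmatory IPSS result does not depend on the footnote. That stands, and it limits the weight of the point. It does not remove it, because sexual function is a named secondary objective and scores that were never collected cannot be recovered later.

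A reader might go further and infer that the remaining comparison is no longer randomised, or is biased. The article does not support that. Bias needs closure to differ by arm in rate or in who closes, and nothing in the article gives a mechanism by which neuromonitoring would change closure. With equal closure in the same kind of patient, the illustration gives zero.

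A reader might also infer that the omitted patients are at higher risk of nerve injury. The Background section lists supra-anal and juxta-anal tumours among the factors that hinder nerve identification, but no section links them to non-closure. The higher risk is an assumption.

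Read literally, the footnote could also cover patients who never had a stoma, who would then lose WVS as well. The abstract counts visits from stoma closure, so the footnote may only replace that schedule where closure has not occurred. The figures are not shown and the wording does not settle the question.

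Nor do the endpoint's closing words, per patient, prove a contradiction. They can describe a within-patient change, and WVS is worded the same way. The accurate statement is that the endpoint is silent on a restriction imposed elsewhere.

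Finally, the omission may be deliberate, for instance because an open stoma was thought to affect sexual function through non-neurogenic routes. The article does not say so. If that is the reason, a split by stoma status would address it and still keep the data.

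**Conclusion.** The point holds in a limited form. The footnote confines the descriptive 12-month sexual-function comparison to patients with stoma closure, a subset formed after randomisation, while the objective, endpoint and analysis sections state no such limit.

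Loss of precision and of generalisability is certain if any stoma stays open. Under an assumed non-closure of 10 to 30%, about 19 to 56 of 188 patients have no sexual-function outcome, and confidence intervals widen by roughly 5 to 20%. Bias between arms is possible but not shown: the illustrated 1.8 to 3.75 points rest on assumed risks of 40% and 70% and on assumed closure differences of 5 to 10 points. The primary analysis is untouched. The change is worth making because the patients are already seen at the right time, but it does not threaten the trial's main conclusion.

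**What to change.** Amend the Fig. 1 footnote so that IIEF/FSFI are collected at the existing 6- and 12-month visits regardless of stoma status, and only WVS is withheld, and only while a stoma is present. This wording also settles the uncertainty about patients who never had a stoma.

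In the analysis, report the sexual-function endpoint by arm, separately for men and women, in all patients with data. Add a descriptive split by stoma status and the non-closure rate in each arm. For patients already past 12 months when the amendment takes effect, report the missing scores by arm, since they cannot be collected retrospectively. If the sponsor prefers to keep the restriction, the minimum is to name the restricted population in the endpoint definition and report non-closure by arm.

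The cost is one added questionnaire at visits already planned, a case report form change, and an amendment across the participating centres. The article lists eight ethics committees. The trial was still recruiting when the article was written, so the change could still benefit later patients.

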### Prescreening / Screening and follow up

In patients undergoing neoadjuvant therapy a prescreening is scheduled 21 to 1 day before therapy begins. The preoperative screening (baseline) is scheduled 14 to 1 day before TME. Study visits and follow up are summarized in Fig. 2.

**Fig. 2 Fig2:**
[figure not shown]
Frequency and scope of study visits

### TME and pelvic intraoperative neuromonitoring

#### Total mesorectal excision

In surgical treatment of rectal cancer, adequate mesorectal excision leads to an optimization of oncologic results. For cancer in the middle and lower rectal third (≤12 cm from the anal verge) a TME is recommended.

#### Neuromonitoring setup

Monitoring of the pelvic autonomic nerves is carried out with a neuromonitoring system (504012 ISIS Touch and accessories, CE 0297, inomed, Emmendingen, Germany), which enables electric stimulation under simultaneous observation of processed EMG signals of the IAS and manometry of the urinary bladder. To observe IAS activity, bipolar needle electrodes (530228, CE 0297, inomed, Emmendingen, Germany) are inserted transanally under endosonographic guidance. The ground electrode (530627, CE 0297, inomed, Emmendingen, Germany) is placed on the left gluteal muscle and the electrodes are connected to the neuromonitoring device. The impedance is measured to ensure correct placement. Simultaneous observation of intravesical pressure is carried out through the transurethral bladder catheter or if applicable suprapubic catheter. The catheter is connected to a pressure transducer (520320, CE 0297, inomed, Emmendingen, Germany), which is linked to the amplifier of the neuromonitoring device. Thereby both measurements could be continuously visualized as neuromonitoring signals online on the screen of the system. Before the onset of neurostimulation the bladder is emptied and filled with 200 ml of Ringers’ solution. Stimulation parameters are set to currents of 1-25 mA, frequency of 30 Hz, and monophasic rectangular pulses with pulse duration of 200 μs.

According to previous investigations a stimulation dependent unilateral or bilateral consecutive increase in intravesical pressure (cmH_2_O) or processed EMG amplitude (V) of IAS will be rated as positive response verifying functional integrity of urinary and anorectal innervation. With regard to sexual function bilaterally observed positive results by manometry and IAS-EMG were valued as preserved genital innervation [5, 6].

#### Pelvic intraoperative neuromonitoring (pIONM)

Stimulation of the pelvic autonomic nerve during mesorectal dissection is performed by the surgeon with a handheld bipolar microfork probe (EW0266 and 522027, CE 0297, inomed, Emmendingen, Germany) and served for identification and verification of functional nerve integrity.

Initial neurostimulations are carried out bilaterally after posterior/posterolateral mesorectal dissection in order to detect the pelvic splanchnic nerves. Therefore, bilateral repetitive stimulations along the pelvic sidewall are carried out (stimulation period 3-10 seconds and resting period in between the stimulations of 3-10 seconds) as a kind of neuromapping under continuous observation of processed IAS-EMG. During ongoing lateral mesorectal dissection neuromapping is performed under simultaneous manometry of the urinary bladder and IAS-EMG for identification of further potentially surgical exposed nervous tissue (pelvic splanchnic nerves S2-4, inferior hypogastric plexus).

Anterolateral mesorectal dissection is performed with neuromapping under continuous processed IAS-EMG. For quality assurance of the nerve-sparing technique after TME (resection of specimen), the autonomic innervation is finally verified by bilateral neuromapping along the pelvic sidewall and just above the pelvic floor under simultaneous manometry of the urinary bladder and IAS-EMG. All observed neuromonitoring signals are manually documented.

For the safety population summaries and listings of safety data will be performed. Frequencies of subjects experiencing at least one adverse event will be displayed by body system and preferred term according to MedDRA terminology. Detailed information collected for each adverse event will include: A description of the event, duration, whether the adverse event was serious, intensity, relationship to trial treatment, action taken and clinical outcome. Summary tables will present the number of subjects observed with adverse events and corresponding percentages. Additional subcategories will be based on event intensity and relationship to trial treatment. A subject listing of all adverse events will be prepared.

For the assessment of oncologic safety the rates of pCRM-positive specimen and the quality of mesorectum will be displayed by means of absolute and relative frequencies separately for each study arm.

### Ethical considerations

#### Assessment of risks and benefits

So far, there were no reports about differences in risk potential for patients undergoing intraoperative electrophysiological confirmation of pelvic autonomic nerves, especially with regard to life threatening events. The individual participant will therefore not run any additional risk during participation in this trial. The potential benefit for the group of patients with additional pIONM is the avoidance of pelvic autonomic nerve damage with maintenance of quality of life, respectively. The intraoperative assessment of nerve-sparing and the predictability of postoperative urogenital and anorectal functional disturbances may offer secondary prevention with the potential for an improved prognosis.

#### Care and protection of research participants

Nerve-sparing TME is a standard treatment for patients with rectal cancer. There are no special adverse events expected. Surrogate parameters of oncologic outcome (rates of R1 and R2 resections, rates of pCRM-positive specimen, and rates of incomplete mesorectal excision) will be closely monitored by the Data Safety Monitoring Board (DMSB). All adverse events and serious adverse events will be recorded. The serious adverse events will be reported within 24 hours of the initial observation to the Interdisciplinary Center for Clinical Trials (IZKS) at the University Medicine of the Johannes Gutenberg-University Mainz, Germany.

### Availability of data and materials

The access to the confident patient information may be granted only to the governmental bodies and authorized representatives of the trial sponsor (clinical monitors). Only patients who explicit consented to these provisions will be enrolled in the clinical trial. The name of the subjects and other confidential information are subject to medical professional secrecy and the regulations of the applicable local data protection regulations. During the clinical trial, subjects will be identified by means of a unique individual identification code (pseudonym). The final trial report, public trial registers as well as scientific publications will solely contain anonymized statistical data.

### Quality assurance / monitoring

The study will be continuously monitored by the clinical research associates of the IZKS. Monitoring will be done by personal visits, telephone and mail contacts by a clinical monitor according to standard operating procedures. All participating centers will be visited by the monitor to ensure compliance with study protocol, good clinical practice and legal aspects.

### Safety

In this trial a DSMB will monitor and supervise the progress of the trial (including the safety data and the critical efficacy endpoints at intervals), review relevant information from other sources, ensure adherence to protocol, advise whether to continue, modify, or stop this trial. Furthermore it will provide the funding organization with information and advice. DSMB will meet annually and on special request. The trial management will organize these meetings and provide all necessary information for the work of the data monitoring board.

### Trial status

The trial is ongoing and in the recruiting phase at the time of manuscript.

## Discussion

The TME within a modern multimodal treatment options for rectal cancer resulted in a tremendous improvement of oncologic outcome and cancer-specific survival while dysfunction rates however remained still high. In consequence maintaining quality of life receives particular attention among colorectal surgeons aiming for best performance of intraoperative nerve-sparing. This is reinforced by the fact that the incidence of colorectal cancer diagnosed in young adults did significantly increase as demonstrated by a recent retrospective cohort study in 393241 patients [18]. Based on current trends it was stated that in 2030, the incidence rate for rectal cancer will increase by 124.2 %, respectively, for patients 20 to 34 years and by 46.0 %, respectively, for patients 35 to 49 years in the United States.

The prerequisite for intraoperative pelvic autonomic nerve preservation is the nerve identification. Only a few authors reported their rather higher or lower nerve identification rates while many others do not specifically provide such information but state its difficulty [3, 19, 20]. In addition to knowledge about aggravating circumstances and confounding factors, the recognition of key zones at risk of harm to the autonomic nerves is another important step for improvement of the nerve-sparing technique regardless of whether TME is performed minimally invasive or open via a transabdominal or transanal approach [21, 22]. In order to master intraoperative nerve-sparing the surgeon must rise to these challenges and take the lead in shifting towards aiming for a more sustainable quality of life.

The start however must be made in the informed consent discussion. A recent survey of rectal cancer patients undergoing surgery demonstrated that about 50 % of patients could not recall a preoperative discussion of risks to urinary, sexual and bowel function. Interestingly, they did desire more information regarding the occurrence of these possible dysfunctions than information on cure rate, need for second surgery, or the ability of surgery to treat their symptoms [23].

The pIONM may offer improvement of intraoperative nerve visualization and could be particularly beneficial with regard to all the confounding factors. Nevertheless, up to now there are no data from prospective randomized studies for comparing the functional outcome after TME for rectal cancer with and without pIONM. The aim of the present study is to evaluate whether pIONM is a valuable method for maintaining patient’s urogenital and anorectal function. This conducted prospective randomized multicenter trial will thereby demonstrate the efficacy, accuracy and safety of pIONM. Furthermore, potential advantages or disadvantages of this method can be analyzed. The study might also help to identify patients who would particularly benefit from pIONM.

With a view to primary prevention, pIONM may represent a useful tool for improvement of the nerve-sparing surgical technique in the minor pelvis. The additional quality assurance of pelvic autonomic nerve preservation after TME with predictability of postoperative urogenital and neurogenic ano(-neo)rectal dysfunctions could serve a secondary preventive function in enabling timely delivered commencement of causal urological-/sexological and proctological treatments with the potential for an improved prognosis in those patients with functional disturbances.

This is the first randomized multicenter trial comparing urogenital and anorectal functional outcome in rectal cancer patients undergoing TME with and without pIONM. If indeed found to be beneficial, pIONM will offer maintenance of patients’ quality of life and possibly decrease the amount of diagnostic and treatment costs of postoperative functional disturbances.

